## Abstract

**Background:**

The transition to college coincides with the peak age of onset for depression and is marked by substantial changes in 24-hour movement behaviors (sleep, sedentary behavior, physical activity). Although these behaviors are modifiable and increasingly implicated in depression risk, most studies rely on cross-sectional, self-reported data and aggregate symptom scores, limiting insight into temporal dynamics and symptom-level heterogeneity. Integrating compositional modeling of 24-hour time use data with network approaches to psychopathology may clarify when and how specific behavioral patterns relate to distinct depressive symptoms during this high-risk developmental window.

**Methods:**

The College Adjustment, Lifestyle and Mental Health (CALM) Study is a 16-week prospective cohort study of 144 first-year undergraduate students (Mage = 18.2 ± 0.4 years; 54.9% female) during their first academic semester. A hybrid panel-burst design combined five monthly panel surveys assessing psychosocial and behavioral factors with five 7-day intensive daily diary assessment bursts distributed across a 108-day period. During each burst, participants completed daily diary adaptations of the PHQ-8 and GAD-7 to capture depressive and anxiety symptoms, along with other contextual variables. Sleep, sedentary behavior, light physical activity, and moderate-to-vigorous physical activity were assessed daily using Fitbit Charge 6 devices. Primary analyses will model daily 24-hour movement behaviors using compositional data analysis to account for the constrained nature of time-use data and integrate these compositions into multilevel vector autoregressive models to estimate within-person temporal, contemporaneous, and between-person associations with individual depressive and anxiety symptoms. Secondary analyses will examine symptom-behavior network differences across movement behavior profiles and assess stability of symptom-behavior networks across the first college term to identify periods of heightened risk for symptom onset and progression.

**Discussion:**

By embedding wearable-derived 24-hour movement behavior compositions within dynamic symptom networks, this study advances precision behavioral psychiatry beyond aggregate depression scores by identifying which behaviors are most strongly linked to specific symptoms, for whom these associations differ, and when risk intensifies during the transition to college. The hybrid panel-burst design further provides a foundation for future predictive modeling of individual risk trajectories and the development of just-in-time adaptive interventions leveraging passive sensing to support early detection and prevention of depression in emerging adults.

## Introduction

College student mental health represents a substantial and growing public health concern. Estimates suggest that between 12% and 50% of college students worldwide experience a mental disorder,^1,2^ a prevalence that exceeds their non-college-attending peers.^2^ Mental health problems are particularly pronounced during the first two years of college, especially during the freshman year, as students navigate a major developmental and contextual transition.^3–5^ This period coincides with the peak age of onset for depression (~ 19.5 years),^6^ further elevating vulnerability among college students. Although symptoms often attenuate by junior year, recent U.S. data indicate that clinically significant depressive symptoms have persisted at rates exceeding 36% since 2018.^7^ Given that nearly two-thirds of U.S. high school graduates enroll in college,^8^ depression during this life stage has important population-level implications, particularly as early-onset depression is associated with elevated risk for recurrence and long-term functional impairment in adulthood.^9^

A substantial body of research has identified modifiable lifestyle behaviors as relevant determinants of mental health during this developmental period.^10–17^ As a result, behavioral approaches are increasingly considered as scalable complements to, or alternatives for, traditional psychotherapy and pharmacological treatments.^18–21^ Physical activity (PA), in particular, has received considerable attention due to its associations with reduced depressive symptoms in young people, including during the transition to college,^13^ with some evidence supporting a causal effect.^22^ However, an exclusive focus on PA provides an incomplete account of daily behaviors that occur within a 24-hour window, as other time-use domains such as sleep and sedentary behavior (SB) also play important roles in shaping mental health.

Over the past decade, there has been a shift from examining PA, SB, and sleep – collectively referred to as 24-hour movement behaviors – in isolation toward an integrated approach that examines all of these behaviors together.^23,24^ The 24-hour movement paradigm emphasizes that the “whole-day” matters for health and acknowledges these behaviors as interdependent components of a fixed 24-hour period. This perspective is reflected in the Canadian 24-Hour Movement Guidelines for Adults, which were the first to provide evidence-based recommendations for how much moderate-to-vigorous PA (MVPA), sleep, and SB adults should engage in over the course of a whole day.^25^ Studies have shown that meeting a greater number of these recommendations is associated with lower levels of depressive symptoms and depression risk.^10,26^ However, reliance on threshold-based guideline adherence obscures substantial within- and between-person variability in movement behavior patterns. For example, individuals who accumulate 150 minutes of MVPA per week are classified as having met this guideline, whereas those accumulating 149 minutes are grouped with individuals reporting no MVPA at all, despite likely meaningful differences in exposure and associated mental health risk based on established dose-response associations.^27^ These limitations are further compounded by widespread use of self-reported measures and cross-sectional designs,^10^ which restrict inferences about temporal dynamics linking 24-hour movement behaviors and depression.

Accurately modeling 24-hour time-use data, therefore, requires analytic approaches that explicitly account for both the continuous nature and interdependence of daily movement behaviors.^28^ Compositional data analysis (CoDA) is an innovative approach commonly used in the field of time-use epidemiology that accounts for the interdependence of time-use components (i.e., PA, SB, sleep) within a constrained 24-hour window, in which time allocated to one behavior reduces time available for others (e.g., increasing PA inherently takes away from time spent in SB and sleep).^29,30^ Unlike traditional statistical models, CoDA accommodates this perfect collinearity in time-use data, minimizing bias and enhancing accuracy.^28,29^ Device-based measures such as actigraphy are particularly well suited to CoDA, as they provide continuous estimates of time spent engaging in sleep, SB, and PA across the entire day. Despite the introduction of CoDA to movement behavior research over a decade ago,^31^ most studies continue to rely on short observational windows (e.g., 7-day accelerometer wear period), obscuring our understanding of the dynamic and evolving nature of these behaviors in relation to depression.^10^

Greater temporal resolution may be critical for elucidating pathways linking 24-hour movement behaviors and depression. Although device-based assessments address key limitations of self-reported PA measures,^32,33^ much of this work has relied on aggregated, low-resolution summaries (e.g., weekly averages) assessed at widely spaced intervals (e.g., baseline, 3 months, 6 months). Only recently have studies begun to leverage high-resolution time series data (i.e., daily summaries across several months) from consumer wearables (e.g., Fitbit, Apple Watch) to characterize long-term behavioral patterns.^34,35^ Employing CoDA with intensive longitudinal device-based data and frequent assessments of depressive symptoms (e.g., multiple weeks of daily diaries) could provide novel insights into within-person associations between 24-hour movement behaviors and depressive symptoms, and how these dynamic relationships evolve as students navigate newfound stressors during the transition to college, while accounting for the inherent measurement properties of 24-hour time-use data.^36^

Advances in analytic methods for time-use data also coincide with broader shifts in how mental disorders are conceptualized. Traditional psychiatric frameworks largely rely on a biomedical approach, viewing disorders as latent disease entities wherein symptoms reflect underlying disease process or common cause.^37^ This approach often models mental disorders as a binary outcome or a sum of symptom severity, treating symptoms as interchangeable and independent.^38,39^ However, symptom presentation varies widely, even within diagnostic categories.^40^ Recognizing this, recent work has reconceptualized mental disorders as emerging from networks of causally interacting symptoms, wherein symptoms influence one another both directly and indirectly, rather than reflecting a common latent cause.^41^ This approach facilitates the study of symptoms as part of a complex and dynamic system involving many interacting elements, offering novel implications for understanding the etiology and course of mental disorders.^42^

Extending mental health symptom networks to incorporate non-symptom risk and protective factors may further enhance their utility. Studies have called for integration of behaviors such as sleep, SB, and PA to better understand the dynamic factors influencing disorder etiology.^43,44^ Doing so may help identify behaviors that exert disproportionate influence on specific symptoms, in addition to revealing self-reinforcing pathways (e.g., insufficient sleep → fatigue → sadness → loss of interest) that represent actionable intervention targets. Although network-based approaches hold promise for advancing precision prevention and treatment strategies, their application to 24-hour movement behavior research for understanding mental health remains limited to date. Addressing this gap will require intensive longitudinal designs that combine extended time-series assessments of 24-hour movement behaviors with repeated measurement of depressive symptoms.

The purpose of this paper is to describe the protocol and baseline characteristics of the College Adjustment, Lifestyle and Mental Health (CALM) Study, an intensive longitudinal cohort study designed to examine dynamic relationships between device-assessed 24-hour movement behaviors and depressive symptoms during the transition to college. Specifically, this study aims to characterize day-to-day associations between 24-hour movement behaviors and individual depressive symptoms, describe movement behavior patterns associated with elevated risk for depressive symptom onset and progression, and identify periods of heightened vulnerability during the transition to college.

## Methods

### Study Design

The CALM Study was a prospective cohort study that followed first-year undergraduate students for 108 days (September 2-December 19, 2025) during their transition into their first academic term at university. Participants were onboarded between August 25 and September 5, 2025. The study employed a hybrid panel-burst design to capture both longer-term changes across the semester and short-term, day-to-day fluctuations in depressive symptoms and 24-hour movement behaviors. This design is consistent with recommendations for measurement-burst designs that integrate intensive short-term assessment within longer-term longitudinal follow-up to distinguish within-person dynamics from broader developmental change.^45,46^

Participants (N = 144) completed five panel surveys administered at four-week intervals following baseline to assess broader psychosocial and contextual factors across the semester. In parallel, five 7-day intensive daily assessment bursts were distributed across the study period (Days 1–21, 22–42, 43–62, 63–82, and 90–108). The intensive burst design was selected as it optimally balances long study windows with reduced participant burden in smartphone-based research.^47^ Burst timing was randomized within predefined calendar windows and did not align systematically with panel survey administration. No bursts were scheduled during Fall break (Days 83–89) to avoid confounding assessments with atypical routines and travel-related disruptions.

To minimize systematic timing effects across the academic term while preserving calendar balance, burst timing was randomized using a constrained block allocation schedule. The 108-day study was divided into five consecutive calendar periods (four 20–21 day windows during the semester and a final 19-day window following fall break). Each period contained three potential 7-day burst windows corresponding to Early, Mid, and Late segments of the period (Fig. 1). Participants were assigned to one of six pre-specified burst sequences (S1-S6), each representing a unique ordering of Early, Mid, and Late burst timing across the five study periods. A fixed set of sequences was used to ensure exact balance across burst positions while maintaining feasibility within the study platform. This allocation scheme was developed to satisfy the feasibility and balance constraints outlined in Table 1.

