#### Aim 3 (Periods of Heightened Risk for Symptom Onset and Progression).

To examine the temporal stability of the depression symptom network across the first college term, including 24-hour movement behaviors and anxiety symptoms as nodes, time-varying network analyses will be conducted using rolling 7-day calendar windows across the 108-day study period.^103^ Although participants contributed data during assigned burst weeks only, pooled daily observations across individuals provide coverage spanning the full academic term. Within each window, mlVAR models will be estimated to derive temporal (lagged) and contemporaneous networks while accommodating the unbalanced repeated-measures structure of the burst design. Window-specific network metrics, including global connectivity (e.g., average edge weight), network density, and node centrality indices, will be computed to evaluate changes in overall interconnectedness and node influence over time. Periods characterized by increased network connectivity or heightened centrality of specific symptoms or behaviors will be interpreted as potential windows of increased vulnerability – or, conversely, relative stability – during the transition to college. Calendar-based academic or institutional events (e.g., midterm periods, finals week, university-designated mental health initiatives such as Wildcat Pause Day) will be descriptively overlaid onto temporal network estimates to contextualize observed patterns.

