As with all longitudinal research in emerging adult populations, several limitations warrant consideration. First, the sample was drawn from a single university and was predominantly White, with relatively few first-generation status college students, which may limit generalizability to more diverse populations of emerging adults transitioning to college. Second, although wearable devices enable continuous free-living monitoring of 24-hour movement behaviors, reliance on proprietary heart rate-informed classification algorithms may introduce measurement imprecision relative to open-source processing of research-grade accelerometry. However, because the present analyses emphasize within-person associations, systematic classification differences are unlikely to meaningfully bias the primary inferences. Third, while mlVAR modeling allows estimation of temporal associations and separation of within- and between-person effects, these analyses do not establish causality; observed lagged relationships should therefore be interpreted as hypothesis-generating. Additionally, although the burst design enhances feasibility and reduces participant burden, intensive symptom assessment occurred during discrete weeks rather than continuously across the semester. As a result, short-lived fluctuations outside burst windows may not have been captured, and temporal inferences rely on pooled observations across individuals. Fourth, daily assessment of suicidality was excluded from the intensive burst protocol due to ethical considerations and the absence of real-time clinical monitoring during unsupervised reporting. Although necessary, this limited examination of the full range of depressive symptoms represented in the PHQ-9 and Diagnostic and Statistical Manual of Mental Disorders, Fifth Edition. Finally, sustained engagement with repeated panel surveys, intensive daily diary bursts, and continuous wearable monitoring across an academic semester may be challenging,^116^ particularly during periods of academic stress or schedule disruption. To mitigate potential attrition and response fatigue, the study incorporated a structured incentive framework, time-limited burst assessments designed to reduce burden, automated reminders within the mobile platform, and routine participant check-ins and personalized prompts delivered by the research team via email.

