## Figures and Tables

**Figure 1 F1:**
[figure not shown]
Daily diary burst timing (Panel A) and randomization schedule (Panel B). Panel A displays the five 7-day burst periods and their timing within the 16-week study, with each period comprising early, mid, and late windows. Panel B illustrates the randomized allocation of burst timing (early, mid, late) for each of the six cohorts (S1-S6) across the five data collection periods (P1-P5).

**Table 1. T1:** Design Constraints and Allocation Properties of the Intensive Burst

Design Constraint	Description
Exact global balance	Across all sequence assignments, Early (E), Mid (M), and Late (L) burst placements occurred equally often.
Exact per-period balance	Within each calendar period, two pre-specified burst sequence groups were assigned to each burst position (E, M, L), ensuring even distribution of assessment load across the five assessment windows.
Participant-level balance	Each sequence maintained a 2-2-1 distribution of burst timing (two assignments to two positions and one to the third), preserving comparable exposure patterns across participants.
Boundary control	Sequences were constructed to eliminate late-to-early transitions across adjacent periods, thereby preventing consecutive burst weeks at period boundaries. This constraint reduced the likelihood of back-to-back assessment weeks, helping to minimize participant burden and support sustained compliance across the semester.
Primacy and recency balance	Two sequences began and two ended with each burst position, reducing systematic timing bias.

**Table 2. T2:** Cohort baseline characteristics.

Participant Characteristics	Mean (SD) or *n* (%)
Age (years)	18.2 (0.4)
Sex (Female)	79 (54.9%)
Race/Ethnicity	
Asian	2 (1.4%)
Black	3 (2.1%)
Hispanic	7 (4.9%)
White	113 (78.5%)
Multiracial	19 (13.2%)
First-Generation Status (Yes)	24 (16.7%)
Parental Education	
Less than high school	1 (0.7%)
High school	11 (7.6%)
Some college/Some University	13 (9.0%)
College/University	62 (43.1%)
Graduate/Professional degree	57 (39.6%)
College of Enrollment	
College of Health and Human Sciences	43 (29.9%)
College of Arts and Sciences	32 (22.2%)
College of Engineering	40 (27.8%)
College of Agriculture	14 (9.7%)
College of Architecture, Planning & Design	6 (4.2%)
College of Business Administration	5 (3.5%)
College of Education	4 (2.8%)
Self-Rated Health	
Fair	16 (11.1%)
Good	54 (37.5%)
Very Good	58 (40.3%)
Excellent	16 (11.1%)
Mental Health Condition Diagnosis	

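### Burst number is exactly aliased with calendar period, so between-period changes in the Aim 3 networks cannot be separated from repeated completion of the same diary

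*Protocol article*

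**What the plan says.** Study Design sets five disjoint calendar periods with one burst per student in each: "five 7-day intensive daily assessment bursts were distributed across the study period (Days 1–21, 22–42, 43–62, 63–82, and 90–108". What is randomised is the slot inside a period: "Burst timing was randomized within predefined calendar windows and did not align systematically with panel survey administration", and "Each period contained three potential 7-day burst windows corresponding to Early, Mid, and Late segments of the period". There are six sequences, "each representing a unique ordering of Early, Mid, and Late burst timing across the five study periods". The stated purpose is: "To minimize systematic timing effects across the academic term while preserving calendar balance, burst timing was randomized using a constrained block allocation schedule". Table 1, under primacy and recency balance, adds: "Two sequences began and two ended with each burst position, reducing systematic timing bias".

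Aim 3 fits networks in rolling 7-day calendar windows pooled over students, and states: "Periods characterized by increased network connectivity or heightened centrality of specific symptoms or behaviors will be interpreted as potential windows of increased vulnerability". The same sentence allows the opposite reading, relative stability.

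The limitations in the Discussion treat repeated assessment as an engagement problem: "To mitigate potential attrition and response fatigue, the study incorporated a structured incentive framework". They do not name it as a rival explanation for change over the term.

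**The concern.** Aim 3 asks when in the first semester students are vulnerable. For that, calendar time has to be distinguishable from other things that change on the same schedule. The obvious one is repetition. By the fifth burst a student has already been asked the same 10 depressive and 6 anxiety items on up to 28 evenings (4 × 7). If repetition alters how items are rated, or how they move together, edge weights and centrality can change without any change in the students' circumstances.

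If some students had their first burst late in the term, the two could be compared. The scheme does not provide that. The primacy and recency constraint balances which slot (Early, Mid or Late) a sequence starts and ends in. It does not balance first against later exposure to the diary. A reader of the article could take the randomisation as protection for early-versus-late-semester comparisons, which it does not give.

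**Working it through.** **Inputs.** From Study Design: periods of Days 1–21, 22–42, 43–62, 63–82 and 90–108; three slots per period; six sequences; onboarding August 25 to September 5; N = 144. From Table 1: two of six sequences in each slot of each period, and no Late-to-Early transitions. From Study Protocol: bursts began September 2, and burst days before enrolment were coded missing for late enrollees in S1 or S2.

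**Reproducing the plan's own figure.** Period lengths are 21 + 21 + 20 + 20 + 19 = 101 days. Adding the 7 break days gives 108, as stated.

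**Aliasing between periods.** One burst per period, in order, means that burst k lies in period k for every student. Write a network metric in period k as μ + C(k) + B(k), where C is the effect of term time and B the effect of burst number. Only the sum C(k) + B(k) is estimable. In a day-level design matrix, intercept plus period indicators has rank 5, and adding burst-number indicators leaves it at 5. None of the 101 covered days has students at different burst numbers. These results need only the disjoint periods, not the exact slot dates.

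**Within a period.** Early, Mid and Late groups share B(k), so it cancels in their difference. With burst number as a factor, a linear calendar-day slope and day-in-burst are still estimable (rank 7 of 7).

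**Size of the layout effect (slot dates assumed).** The slot dates are in Figure 1, which is not shown. I assume Early = first 7 days, Late = last 7 and Mid = centred, so starts are Days 1/8/15, 22/29/36, 43/50/56, 63/70/76 and 90/96/102.
- Mean diary day per period: 11, 32, 52.67, 72.67, 99; grand mean 53.47.
- Between-period variance: (42.47² + 21.47² + 0.80² + 19.20² + 45.53²)/5 ≈ 941.4.
- Within-period variance: slot starts (32.67 + 32.67 + 28.22 + 28.22 + 24)/5 = 29.16, plus 4 for day-in-burst, = 33.16, so SD ≈ 5.8 days.
- Share between bursts: 941.4/(941.4 + 33.16) ≈ 0.966.

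**Device age.** Issue dates span 12 days, so on any date device age differs by at most 11 days. The correlation of device age with calendar day is √[V/(V + v)], with V ≈ 974.5 and v the variance of issue dates. Uniform issue dates give v = (12² − 1)/12 = 11.9 and r ≈ 0.994. Half on the first and half on the last date gives v = 5.5² = 30.25 and r ≈ 0.985. This is nearly collinear but not aliased.

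**What within-period contrasts leave open.** On the assumed dates, a period-2 Early burst (start Day 22) follows the previous start by 14 or 21 days, because Late-to-Early is barred. A Late burst (Day 36) follows by 21, 28 or 35. The groups share burst number but differ in days since the last burst. In period 1, September 5 is Day 4, so late enrollees in S1 or S2 can lose the first few days.

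**Students in and out of burst.** With equal sequences, each slot holds 144 × 2/6 = 48 students. On the assumed dates, slots overlap on 4 days (56, 76, 96, 102). On the other 97 of 101 covered days, about 48 students are in burst and 96 are not, all assigned to wear the device.

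**The case against.** Several counter-arguments have force.

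- **The randomised placement is not idle.** A reader might infer that Aim 3 makes no use of it. In fact the rolling windows are calendar windows, and inside a period they move through the Early, Mid and Late groups. A peak within Days 90–108, say, is compared with other windows at the same burst number. This stands. What is missing is a distinction between such contrasts and between-period ones.
- **Aim 3 interprets network metrics.** A fall in reported symptom level is not what the plan reads as vulnerability, and the article gives no basis for saying how far repetition would change edges. This stands; the point concerns identifiability, with no known size of bias.
- **The language is already cautious.** Windows are called potential, events are overlaid descriptively, and lagged relationships are called hypothesis-generating. True, but those cautions concern causality and pooling. None names repeated assessment.
- **The wording on timing is loose more than false.** Study Design says that timing is randomised within calendar windows, and Table 1 speaks of burst position. It would be too strong to say that the article claims to separate burst order from term time.
- **One entering class ties study time to term time.** This is inherent for device age and the common start. It is not inherent for burst number, which follows from giving every student one burst in every period, a reasonable choice that still limits what can be concluded.

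**Conclusion.** The point holds for between-period changes in the Aim 3 network metrics: burst number and calendar period are exactly aliased, and no amount of data resolves that. It does not extend to within-period contrasts, where burst number is constant. For device novelty the relation is near-collinearity (r about 0.985 to 0.994, assuming issue dates unrelated to sequence), and it arises from the common start, not the burst scheme.

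The figure of about 97% describes the geometry under assumed slot dates. A reader might take it as the share of an observed change due to repetition, and the documents support no such reading. The primary hypotheses, on within-person daily associations (Sample Size Calculation), are not challenged here. This is a cheap improvement: followed as written, Aim 3 could attribute a repeat-assessment change to the semester.

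**What to change.** 1. **Aim 3.** Base statements about windows of vulnerability on formal Early/Mid/Late contrasts within a period. Note that these groups still differ in days since the last burst, and that some S1/S2 days in period 1 are missing for late enrollees. Because students received pre-randomised study numbers according to their chosen timeslot, check baseline balance across sequences. Label between-period differences descriptive and inseparable from repeated assessment.
2. **Added check.** Compare Fitbit composition between in-burst and not-in-burst students on the same calendar days. This tests whether the diary changes behaviour. It does not test drift in symptom reporting.
3. **Study Design and Table 1.** State that the scheme balances burst position within periods, not burst order across the term.

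The cost is two analyses of data already collected and some rewording. Early-versus-late-semester statements become descriptive. The within-period contrasts rest on about 48 students per slot with at most 7 days each (48 × 7 = 336 diary days), so their precision should be reported with them.
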